### Intervention

All participants will first receive a standardized 30-min health education session covering sarcopenia, healthy lifestyle practices, and nutrition-related prevention strategies. Before intervention delivery, caregivers assigned to the exercise groups will undergo centralized training by exercise specialists to ensure standardized implementation across residential buildings. Usual medical care and routine nursing home services will continue throughout the trial in all groups. Participants will be asked not to initiate any additional structured exercise programme outside the study during the intervention period. Any relevant changes in health status, medication use, or rehabilitation participation will be documented where feasible.

To minimize contamination across groups, exercise sessions will be delivered within the assigned residential buildings and scheduled separately by group. Caregivers involved in intervention delivery will be assigned to specific buildings during scheduled sessions, and group-specific exercise materials will not be shared across groups. Participants will be asked not to attend sessions assigned to other groups. Any additional rehabilitation, structured exercise, or cross-group exposure will be recorded through caregiver logs, participant reports, and process evaluation activities [39].

The intervention is designed as a 48-week pragmatic, group-based exercise programme delivered within participants’ residential buildings. Exercise sessions will be conducted three times per week, with each 45-min session comprising a 10-min warm-up, a 30-min core exercise component, and a 5-min relaxation period. To enhance feasibility in routine nursing home care, the programme will be delivered using pre-recorded specialist-led videos and supervised through a phased model in which specialist involvement is progressively reduced and caregiver-led delivery correspondingly increased over time.

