During weeks 1–12, specialists will provide on-site supervision for all sessions alongside caregivers. During weeks 13–24, on-site supervision will be reduced to one randomly scheduled visit per week, with the remaining sessions supported remotely. During weeks 25–48, sessions will be primarily supervised by caregivers using the video-guided materials, while specialists continue to provide remote oversight. Attendance at each scheduled exercise session will be recorded electronically by caregivers and summarized as an adherence and feasibility indicator; detailed attendance definitions and calculation procedures are provided in Additional file 1.

Adherence support will be guided by the Capability, Opportunity, Motivation–Behaviour (COM-B) model [40], and the Theoretical Domains Framework (TDF) [41] targeting exercise adherence in participants. Specifically, delivery within participants’ residential buildings, small-group sessions, caregiver assistance, and specialist supervision will target physical and social opportunity; health education, video-guided instruction, and seated exercise formats will target psychological and physical capability; and attendance monitoring, supportive feedback, low-value attendance-based incentives, and public recognition of highly engaged participants who consent to being acknowledged will target reflective and automatic motivation through reinforcement, self-efficacy, social norms, commitment, and habit formation [42].

Intervention sessions may be modified or temporarily discontinued for individual participants in the presence of acute illness, pain exacerbation, dizziness, chest discomfort, marked fatigue, participant refusal, or any other condition judged by caregivers or supervising staff to make continued exercise unsafe. Participants who discontinue the intervention will be encouraged to remain in outcome assessments whenever possible. Detailed intervention procedures are presented in Fig. 2 and Additional file 1.

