#### Secondary outcomes

Timed Up and Go Test.The Timed Up and Go (TUG) test will be used to assess functional mobility and fall risk [45]. Participants will be instructed to rise from a standard armchair (seat height 43–45 cm), walk at their usual pace for 3 m, turn around, return to the chair, and sit down.Balance Performance.Standing balance will be assessed using a modified Clinical Test of Sensory Integration for Balance on a Wii Fit Balance Board (Nintendo Co., Ltd., Kyoto, Japan), with center-of-pressure displacement derived from standardized stance conditions: 1) side-by-side, eyes open, 2) side-by-side, eyes closed and 3) semi-tandem, eyes open [46].Physical Activity and Sedentary Behavior patterns.PA and sedentary behaviour will be assessed using both objective monitoring and self-report. Objective data will be collected using a thigh-worn Fibion accelerometer (Fibion Inc., Jyväskylä, Finland) to characterize daily sedentary time and activity intensity [47, 48]. Participants will be asked to wear the device continuously 24 h/day over 7 consecutive days at each assessment time point [49, 50]. A valid assessment will require at least three valid days with a minimum predefined wear duration per day. Self-reported activity and sedentary behaviour over the preceding week will be assessed using the short form of the International Physical Activity Questionnaire (IPAQ-SF) [51].Neuromuscular Activation.Neuromuscular activation will be assessed using a wearable textile surface electromyography (sEMG) system (MSleeve, Myontec Ltd., Kuopio, Finland) [52–54]. Recordings from the tibialis anterior, gastrocnemius, and soleus muscles will be obtained during the GS test, 5STS test, TUG test, and standing balance assessment to examine exercise-related changes in lower-limb motor control. Predefined exploratory sEMG variables will include task-specific muscle activation amplitude, activation duration, and, where feasible, muscle co-activation patterns during functional tasks. Raw signals will be processed using standardized filtering, artefact removal, and normalization procedures specified before analysis.Biological Specimen Collection.At baseline and week 48, participants will be instructed to provide approximately 5 mL of saliva in a sterile collection tube, excluding froth. Prior to sample collection, participants will be asked to refrain from eating or drinking for 1–2 h to minimize contamination and ensure sample quality, following established saliva collection protocols [55]. All biospecimens will be stored at 4 °C in insulated containers for no more than two hours before transportation to the biochemistry laboratory at Zhejiang University for processing. Saliva samples will be centrifuged at 3,000 rpm for 10 min to separate cellular debris from the supernatant, following standard procedures for saliva sample preparation and biobanking [56]. The resulting fractions will be aliquoted into EP tubes. All processed samples will be stored at -80°C until omics profiling is conducted.Saliva-derived DNA will be extracted for telomere length measurement and DNA methylation analyses. Saliva provides a practical and non-invasive source of genomic DNA for large-scale population studies and has been widely used in aging research [57]. Telomere length is a well-established biomarker of cellular aging [58, 59], whereas DNA methylation profiles capture age-related epigenetic alterations and can be used to derive measures of biological aging, such as epigenetic clocks [60, 61]. Integrating these measurements provides complementary information on biological aging processes and may help elucidate mechanisms underlying age-related health outcomes and functional decline [57, 61].Questionnaire-Based Assessments.Questionnaire-based assessments will be used to evaluate cognition, mental health, sleep quality, frailty, health-related quality of life, functional independence, traditional Chinese medicine constitution, perceived physical activity needs, and adverse childhood experiences, using validated instruments including the CMMS, MoCA, GDS-15, GAD-7, PSQI, CFS, SF-36, ADL scale, CCMQ, and ACE-based indicators [62–71].Clinical Events and Care-dependency.Impaired mobility and sarcopenia-related functional decline are associated with adverse health outcomes, falls, increased healthcare utilization, and care dependency in nursing home residents [72, 73]. Therefore, clinical event records and care-dependency level will be collected through continued collaboration with the nursing home and verified using routine institutional records where available. Baseline clinical event records will capture pre-trial event history, including prior hospitalization or emergency transfer, falls, and injurious falls. During the 48-week intervention period, subsequent clinical events, including all-cause mortality and recorded cause of death, hospitalization or emergency transfer and corresponding reasons, falls, and injurious falls, will be continuously recorded and summarized at Week 12, Week 24, and Week 48. During the post-intervention follow-up period, the same clinical events will continue to be recorded and summarized at 1 and 2 years post intervention. Care-dependency level will be recorded at baseline, Week 12, Week 24, Week 48, and 1 and 2 years post intervention using routine nursing-care registration records [32].

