A comprehensive assessment framework will be applied to capture both clinical effectiveness and underlying mechanisms of action. In contrast to prior studies relying on single-domain endpoints [85, 86], the primary outcome is a composite Z-score integrating muscle mass, strength, and physical performance, thereby providing a continuous measure of sarcopenia severity. To account for potential compensatory reductions in daily activity [87], accelerometer-based monitoring will be implemented at multiple time points to quantify overall activity changes and examine their moderating effects [87, 88]. The assessment strategy is further extended to include surface electromyography and center of pressure measures of standing balance in order to elucidate neuromuscular adaptations associated with different exercise modalities [89]. In particular, saliva-derived DNA will be utilized for telomere length determination and methylation analyses, providing accessible biomarkers for aging-related molecular adaptations to exercise [90–92].

Several limitations must be acknowledged. While the SCOPE study will be conducted in the largest nursing home facility in the region, the single-centre design may affect the generalisability of the results. Because reliable ICC and effect-size estimates for the proposed composite sarcopenia Z-score in oldest-old nursing home residents are limited, the sample-size calculation should be interpreted as a pragmatic planning estimate. The study may be underpowered to detect small between-group effects, and the observed ICCs and cluster sizes will be reported to inform future definitive trials. The 48-week intervention period, while necessary for assessing long-term effects and accounting for seasonal variation [93], could increase the risk of attrition due to health deterioration, institutional transfers, or temporary facility closures. To mitigate these challenges, the protocol incorporates adaptive strategies such as intervention period extension, home-based exercise guidance, and optional live-streamed sessions to support continued participation during absences. Additionally, to better simulate real-world staff turnover and resident mobility, the recruitment in predefined waves may be implemented as needed. This flexible approach ensures that the trial can adapt to the dynamic nature of nursing home environments.

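### Whole-day accelerometer totals mix the study's own exercise sessions with the everyday activity in which compensation would show

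*Protocol article*

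**What the plan says.** The Discussion gives the reason for accelerometry and the quantity in one sentence: "To account for potential compensatory reductions in daily activity [87], accelerometer-based monitoring will be implemented at multiple time points to quantify overall activity changes". The sentence goes on to plan a look at how those changes moderate effects. The same whole-day change is therefore both the quantity reported and the moderator.

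Under Secondary outcomes the device is worn on the thigh and is used "to characterize daily sedentary time and activity intensity". On wear, "Participants will be asked to wear the device continuously 24 h/day over 7 consecutive days at each assessment time point". On completeness, "A valid assessment will require at least three valid days with a minimum predefined wear duration per day". Nothing in the article separates session time from the rest of the day, or says which days must be valid.

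Under Intervention, "Exercise sessions will be conducted three times per week, with each 45-min session comprising a 10-min warm-up, a 30-min core exercise component", followed by 5 minutes of relaxation. The Control group section gives that arm no exercise from the study. The Modified Baduanjin group section describes a seated programme; the Resistance training group section states no posture. Table 1 places activity assessment at baseline, Weeks 12, 24 and 48, and Years 1 and 2.

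Also under Intervention, "Attendance at each scheduled exercise session will be recorded electronically by caregivers". The article describes that record only as an indicator of adherence and feasibility.

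**The concern.** The stated target and the stated quantity differ. A resident who adds study sessions but walks less for the rest of the day is compensating, and the whole-day total nets one against the other. Only the exercise arms have sessions, and only while the programme runs, so the netting differs between arms and between waves.

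Three readings are at risk:

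- **Between arms.** A similar whole-day total in exercise and control arms at Week 12 or 24 could be reported as no compensation although non-session activity had fallen.
- **Over time.** A drop from an in-programme wave to Year 1 could be read as lost everyday activity when it is only the sessions ending.
- **Moderation.** Whole-day change partly reflects how many sessions a resident attended in the wear week. A moderator effect could then reflect exercise dose received, not behaviour outside the sessions.

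**Working it through.** The article gives no figure for this point, so there is none to reproduce. The check sizes the session time contained in the whole-day measure.

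**Inputs from the article**

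- Exercise arms: 3 sessions/week, 45 min each, of which 30 min is core exercise (Intervention).
- Control arm: 0 min/week of study exercise (Control group).
- Wear: 7 days requested, at least 3 valid days accepted (Secondary outcomes).
- Waves: Weeks 12 and 24 lie inside the 48-week programme; baseline and Years 1 and 2 contain no sessions. The article does not say whether the Week 48 wear precedes the last session.

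**Assumptions of this check**

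- Attendance of 40–80% as an illustrative range, besides full attendance.
- A true fall of 15 min/day in non-session activity, as an example.
- For the valid-day check, three session days among seven, with the valid days a random subset and full attendance.

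**1. Session time per day = sessions × minutes ÷ 7**

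| | Whole session | Core only |
|---|---|---|
| Per week | 3 × 45 = 135 min | 3 × 30 = 90 min |
| Per day, full attendance | 135/7 = 19.3 min | 90/7 = 12.9 min |
| Per day, 80% attendance | 15.4 min | 10.3 min |
| Per day, 40% attendance | 7.7 min | 5.1 min |
| Control arm | 0 | 0 |

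**2. If sessions register as activity.** Apparent whole-day change = session time − true fall. With a true fall of 15 min/day and full attendance:

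- whole session registers: 19.3 − 15 = +4.3 min/day, the opposite sign to the true change in non-session activity;
- core only registers: 12.9 − 15 = −2.1 min/day, a fraction of the true fall.

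**3. If seated sessions are read as sitting.** Up to 19.3 min/day of exercise is then recorded as sedentary time. Where a session displaces time that would have been upright, this appears as added sedentary time and may look like compensation.

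**4. Can the known dose simply be subtracted?** In part. With no compensation, the total should rise by 19.3 min/day if the whole session registers at full attendance. That expected rise is 12.9 if only the core registers, a gap of 19.3 − 12.9 = 6.4 min/day. At 40% attendance it is 7.7, a gap of 19.3 − 7.7 = 11.6 min/day. The attendance record can close the second gap. It cannot close the first, which depends on what the device records during a session.

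**5. Three-valid-day rule.** The probability of capturing k sessions in 3 valid days is C(3,k) × C(4,3−k) ÷ C(7,3):

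| Sessions captured | 0 | 1 | 2 | 3 |
|---|---|---|---|---|
| Probability | 0.114 | 0.514 | 0.343 | 0.029 |
| Session min/day | 0 | 15 | 30 | 45 |

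The mean is 19.3 min/day, as for a full week, with SD 10.5. On these assumptions the rule adds noise in the exercise arms, not systematic bias.

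**The case against.** The strongest reply is that removing session windows is a data-processing rule of the kind an analysis plan or supplement commonly holds. Neither the analysis plan nor Additional file 1 is at hand, and either could contain such a rule. That stands as a limit: a reader might infer that no rule exists, and the article does not show that. The point is narrower. The article itself names a quantity, whole-day change, that does not isolate the target it gives as the reason for measuring.

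Second, whole-day activity is a legitimate outcome, since it answers whether residents become more active on balance. This is right, and the outcome should stay.

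Third, a reader might infer that compensation is invisible or that the stated purpose cannot be met. That goes too far. The session dose is fixed, attendance is recorded, and there are baseline and concurrent control measurements, so a shortfall against the expected rise is informative. What remains is uncertainty about how much of a session the device registers.

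Fourth, the size and direction are conditional, and a reader might infer a known difference in distortion between exercise arms. The documents do not support that. The article gives no posture for the resistance sessions and does not say how the device classifies seated or elastic-band movement.

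Fifth, the span of 0 to 45 min/day under three valid days is an extreme of the minimum-wear case and should not be quoted as the size of a bias.

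**Conclusion.** The point holds as a mismatch between purpose and measure, in a secondary outcome and its moderator use. At Weeks 12 and 24, and at Week 48 if wear precedes the last session, whole-day data in the three exercise arms contain up to 135 min/week of study sessions. That is 19.3 min/day at full attendance, 12.9 if only the core registers, and proportionately less at lower attendance. Control, baseline and Years 1 and 2 contain none.

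Whether this hides compensation or imitates it depends on how the device classifies the sessions, which the documents do not state. The example of a 15 min/day fall appearing as +4.3 rests on sessions registering fully as activity and on full attendance.

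The composite sarcopenia Z-score, its model and the sample size are unaffected. The valid-day rule is a minor point. The change is worth making before data collection because session times that are not logged may not be recoverable afterwards.

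**What to change.** 1. Have caregivers enter each session's start and end time with the electronic attendance record.
2. Define the compensation outcome, and the moderator, as non-session activity and non-session sedentary time. At in-programme waves, remove the windows of sessions the resident attended.
3. Apply matching clock windows to control residents, and to baseline records where change from baseline is analysed, so that the same parts of the day are compared. Expressing results per hour of remaining wear time handles unequal durations. Because attendance is itself a post-randomisation variable, a sensitivity analysis that removes all scheduled windows regardless of attendance is sensible.
4. Keep whole-day activity and sedentary time as a separate outcome, described as net activity.
5. State whether the Week 48 wear week falls before the last session.
6. As a minor addition, report how many session days each valid record contains.

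If the analysis plan or Additional file 1 already contains such a rule, it is enough to bring the article's wording into line with it.

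The cost is a small logging burden for caregivers, some analysis code, and slightly less wear time in the compensation outcome. No extra visit or device is needed.

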**Methods:**

This pragmatic, cluster-randomized controlled trial aims to recruit 104 residents aged ≥ 75 years with sarcopenia from a large nursing home in Hangzhou, China. Participants will be randomized by residential building into four groups: Modified Baduanjin Group, Resistance Training Group, Combined Exercise Group, and Control Group. The 48-week intervention will be delivered by trained caregivers using video-guided sessions, with phased reduction in specialist supervision. The primary outcome is a composite sarcopenia Z-score integrating handgrip strength, Short Physical Performance Battery, and appendicular skeletal muscle mass index. Secondary outcomes include functional mobility, balance, physical activity and sedentary behaviour, neuromuscular activation, questionnaire-based assessments, and saliva biological markers. Clinical events and care-dependency records will also be collected throughout the intervention and follow-up periods. Assessments will be conducted at baseline, week 12, week 24, week 48, and at 1 and 2 years post-intervention.

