### Outcome assessment

Outcome assessments are scheduled to evaluate both short-term intervention effects and the maintenance of longer-term benefits. With the exception of biospecimen collection, the outcomes will be assessed at baseline, weeks 12, 24, and 48, and again at 1-year and 2-year post-intervention follow-up. HG will additionally be measured every 4 weeks during the intervention period to capture more continuous changes in muscle strength, whereas biospecimens will be collected at baseline and week 48 only. The full assessment schedule is summarized in Table 1.

**Table 1 Tab1:** Schedule of study assessments

Measure	Screening	Baseline	Intervention												Follow-up	
		**Week 0**	**Week 4**	**Week 8**	**Week 12**	**Week 16**	**Week 20**	**Week 24**	**Week 28**	**Week 32**	**Week 36**	**Week 40**	**Week 44**	**Week 48**	**Year 1**	**Year 2**
Primary outcomes																
Sarcopenia Z-score	** × **	** × **			** × **			** × **						** × **	** × **	** × **
Components																
ASMI	** × **	** × **			** × **			** × **						** × **	** × **	** × **
HG	** × **	** × **	** × **	** × **	** × **	** × **	** × **	** × **	** × **	** × **	** × **	** × **	** × **	** × **	** × **	** × **
SPPB	** × **	** × **			** × **			** × **						** × **	** × **	** × **
Secondary outcomes																
TUG		** × **			** × **			** × **						** × **	** × **	** × **
PA level		** × **			** × **			** × **						** × **	** × **	** × **
sEMG		** × **			** × **			** × **						** × **	** × **	** × **
Balance function		** × **			** × **			** × **						** × **	** × **	** × **
Sample collection		** × **												** × **		
Questionnaires		** × **			** × **			** × **						** × **	** × **	** × **
Clinical events		** × **			** × **			** × **						** × **	** × **	** × **
Care-dependency		** × **			** × **			** × **						** × **	** × **	** × **

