### Statistical analysis

All analyses will follow the intention-to-treat (ITT) principle, including all randomized participants in their assigned groups regardless of adherence or withdrawal [75]. Data will be stored in a password-protected database and managed by designated research staff. Analyses will be performed by an independent statistician using R software (R Foundation for Statistical Computing, Vienna, Austria).

Baseline characteristics will be summarized using descriptive statistics. Continuous variables will be presented as mean ± SD or median [IQR], as appropriate, and categorical variables as frequencies and percentages. Baseline balance across groups and clusters will be descriptively assessed.

Primary and secondary continuous outcomes will be analyzed using linear mixed-effects models, with fixed effects for group, time, and group-by-time interaction, and adjustment for the baseline value of the corresponding outcome and relevant covariates where appropriate. Random intercepts for residential building clusters and participants will be included to account for cluster randomization and repeated measurements. The main intervention effect will be estimated from the group-by-time interaction, with Week 48 as the primary endpoint. Bonferroni-adjusted post-hoc comparisons will be conducted where appropriate. Binary or categorical outcomes, including adverse events, will be analyzed using generalized linear mixed models. Long-term clinical events and care-dependency records will be summarized descriptively by group, with exploratory cluster-adjusted analyses conducted if event numbers permit.

Model assumptions will be assessed using residual diagnostics, and transformations or robust methods will be considered if needed. Missing outcome data will be handled using multiple imputation under the missing-at-random assumption. Sensitivity analyses will compare the intention-to-treat results with per-protocol and complete-case analyses. Effect sizes will be reported as standardized mean differences for continuous outcomes and odds ratios for binary outcomes. Statistical significance will be set at a two-sided α = 0.05.

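### Change in physical activity is named as an effect moderator, although it is measured after randomization and the programme is expected to alter it, so comparing arms by activity change is not protected by randomization

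*Protocol article*

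**What the plan says.** The Discussion explains why activity is monitored. The reason given is "To account for potential compensatory reductions in daily activity", and the plan is that "accelerometer-based monitoring will be implemented at multiple time points to quantify overall activity changes and examine their moderating effects". Grammatically, the thing whose moderating effects are examined is the change in activity, not its baseline level.

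Elsewhere the article treats activity as an outcome:

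- Abstract, Methods: "Secondary outcomes include functional mobility, balance, physical activity and sedentary behaviour".
- Outcome assessment: "the outcomes will be assessed at baseline, weeks 12, 24, and 48", with two later follow-ups. Table 1 marks activity at week 0 and at each of these visits.
- Secondary outcomes: "Objective data will be collected using a thigh-worn Fibion accelerometer", worn "over 7 consecutive days at each assessment time point".
- Intervention: "Exercise sessions will be conducted three times per week". The control arm receives no exercise sessions from the study.

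The Statistical analysis section specifies mixed models with "fixed effects for group, time, and group-by-time interaction". It describes no moderation or mediation model, so nothing there redirects the statement in the Discussion.

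**The concern.** A moderator analysis in a randomized trial asks whether the treatment effect differs between kinds of resident. Randomization supports that comparison when the kinds are defined by something allocation cannot influence, such as a baseline value. Activity change is defined after allocation. The protocol expects exercise to reduce residents' other activity, and the wear week can include the study's own sessions in the exercise arms only. Residents with the same activity change in two arms may therefore differ in health, and a contrast between them mixes the effect of exercise with that difference.

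At stake is a conclusion such as: exercise helps less in residents who compensate by moving less. The question behind that conclusion, whether compensation erodes the benefit, is one of mediation. A group-by-activity-change term does not answer it without further assumptions.

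**Working it through.** The article gives no figure for this analysis, so there is none to reproduce. The check is to ask when conditioning on activity change misleads, and by how much under stated assumptions.

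**Set-up (all values assumed).** Health U has variance 1 and is unmeasured. Activity change is M = a·U + shift·group + noise of variance 1, where a may differ by arm. The outcome is Y = effect·group + b·U + noise. The treatment effect is constant and M has no effect on Y, so any interaction found is false.

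**Formula.** Within an arm, the slope of Y on M is b·a/(a² + 1). The false interaction is the exercise slope minus the control slope.

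With b = 0.6:

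| a, control | a, exercise | slope, control | slope, exercise | false interaction |
|---|---|---|---|---|
| 0.2 | 0.8 | 0.12/1.04 = 0.115 | 0.48/1.64 = 0.293 | 0.177 |
| 0.5 | 1 | 0.30/1.25 = 0.24 | 0.60/2 = 0.30 | 0.06 |
| 0.8 | 1.25 | 0.48/1.64 = 0.293 | 0.75/2.5625 = 0.293 | 0 |

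Over these three pairs the result runs from 0 to about 0.18 per unit of M. It can be zero even when the arms differ, and it is always zero when a is equal in both arms.

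**Simulation.** Here b = −1, so better health lowers the score, as with the protocol's Z-score, where higher is worse. The true effect is −1.0 and the shift in mean activity is −0.5. Two arms were fitted by ordinary least squares without clustering, with 4,000 trials per cell. Group sizes are 26, the enrolment target, and 18, from 26 × 0.7 = 18.2 after the stated 30% dropout. The interaction is tested at the protocol's two-sided 0.05.

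| a, control | a, exercise | interaction by formula | simulated mean (26) | rejected, 26 per group | rejected, 18 per group |
|---|---|---|---|---|---|
| 0 | 0.5 | −0.40 | −0.39 | 16.9% | 13.8% |
| 0 | 1 | −0.50 | −0.50 | 32.9% | 23.3% |
| 0.2 | 1 | −0.31 | −0.31 | 16.2% | 12.8% |
| 0.5 | 1 | −0.10 | −0.10 | 7.2% | 6.0% |
| 0.5 | 0.5 | 0 | 0.01 | 4.9% | 5.5% |
| 0 | 0 | 0 | 0.01 | 4.6% | 4.6% |

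These interactions are larger than those in the first table because b and the slope pairs differ. In the first four rows the false interaction does not shrink with sample size: at 2,000 per arm it is rejected in 83% to 100% of trials.

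**Equal slopes with a mean shift (0.5, 0.5).** The interaction test keeps its size, but the group effect adjusted for M does not stay at −1.0. The slope of Y on M is −0.5/1.25 = −0.4, so the adjusted effect is −1.0 − (−0.4)(−0.5) = −1.2. The simulation gives −1.21 at 26 per group and −1.20 at 18.

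**No link to health (0, 0).** The adjusted group effect is −0.99 at 26 per group, so there is no bias. With no mean shift either, which is the situation of a moderator fixed before randomization and unrelated to prognosis, rejection is 4.8% at 26 per group and 5.3% at 18.

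**The case against.** The statement is one clause in the Discussion, in a paragraph on why measures were chosen. No group-by-activity-change model is written down, and an analysis plan that is not shown could define the analysis differently. The word moderating may loosely mean attenuating, since the paragraph is about mechanisms; the two studies cited at that point cannot be consulted here. Effect modification by a post-randomization variable can also be studied under explicit extra assumptions. Activity change is already a secondary outcome, to be compared by arm in the mixed model, so part of the remedy is in place.

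Much of this stands, and it keeps the point small. It does not remove it: the clause says what will be examined and names activity change as the moderator, and no other section corrects that. This is a stated choice, not an omitted detail.

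A reader might infer that because residents in failing health both move less and score worse, an interaction test would necessarily report false moderation. That does not follow. Confounding by health that is equal in both arms produces a main effect of activity, not an interaction; its bias falls on the adjusted group effect when the programme shifts mean activity. A false interaction needs the link between activity change and health to differ by arm. The documents give no figure for that link, so no single magnitude should be quoted as expected. The planned adjustment for the baseline outcome, left out of the illustration, could also absorb part of the confounding.

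**Conclusion.** The point holds as a minor correction to one exploratory analysis. The article proposes to examine moderation by a variable that it also treats as a consequence of the intervention, and randomization does not protect that comparison. The possible results are a false interaction, a biased conditional group effect or no bias, depending on how activity change relates to prognosis in each arm. Under the assumed values, the false interaction is 0 to about 0.18 per unit with the 0.6 health coefficient and the three slope pairs shown. In the simulation, pairs with unequal slopes raise false-positive rates to 7% to 33% at 26 per group and 6% to 23% at 18, against a nominal 5%. These are illustrations, not forecasts.

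A reader might also infer that the trial's main result, or its guidance on exercise, is compromised. The documents do not support that. The Week 48 primary comparison and the between-group estimates for secondary outcomes do not condition on activity change, and the article ties its intended guidance to the trial's findings in general.

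**What to change.** In the Discussion, replace moderation by activity change with three separate statements.

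1. Effect modification is examined by baseline accelerometer activity, which Table 1 already schedules at week 0.
2. Activity change is reported by arm, as the secondary outcome it already is.
3. If compensation is of interest, activity change at week 12 or 24 is examined as an exploratory mediator of the Week 48 outcome, with named confounders and a sensitivity analysis for unmeasured confounding.

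The cost is a change of wording and, if the third item is wanted, a short specification. No new data or visits are needed. The downside is that the mediation analysis rests on assumptions that the data cannot test, so it must be labelled exploratory. Baseline activity also answers a different question, namely whether residents who are more active at entry benefit differently; it does not stand in for the compensation question.
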